### Secondary Outcome:

The change in SBP will be the secondary outcome. Two readings will be taken, and the final measurement is the average of the two. Systolic blood pressure will be assessed at baseline and six months.

### Sample Size:

The sample size is calculated using the Lemeshow et al. 1990s formula: 
[figure not shown]
17 to detect between the two groups on the adherence change to the primary outcome measure. The adherence score in the intervention group is 7.4, and in the control, it is 7.0.^18^. The alpha level is set at 0.05, a confidence interval of 95%. The calculated sample size is 220 in each group and 440 overall after a 30% attrition rate.

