### Outcome Measures

### Primary Outcome:

The change in adherence to antihypertensive medication will be the primary outcome. The primary endpoint will be assessed using the SEAMS and pill counts used over a certain period.^14^,^16^ The adherence to antihypertensive medication will be assessed at baseline and six months.

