### Data Collection:

A four section validated and pretested questionnaire in Urdu and English will be utilized. Section-A will involve the collection of data on pertaining to health and sociodemographics. Section B will be the the SEAMS-related scale.^20^ A 13 item measure called SEAMS is used to evaluate medication adherence.^20^ The scale’s scores go between 13 and 39. Greater levels of scores are correlated with better scores.

In Section-C, participants will be questioned about the number of pills used. The number of tablets taken over a certain time period divided by the total number of tablets prescribed for that time period was used to calculate the non-adherence rates.^16^ If the adherence percentage is 80% or higher, it will be considered adherent; if it is less than 80%, it will be regarded non-adherent. The literature also reports on this threshold. 14,16

Finally, Section-D will be a survey of the post-intervention follow-up to determine the intervention’s acceptability. At the final follow-up interview, participants in the intervention arm will be evaluated for end-user suggestions.

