### Statistical Analyses:

Intention-to-treat analysis will be applied. The mean and standard deviation/ median and interquartile ranges will be presented. Frequencies and percentages will be used to depict categorical data. Differences in adherence scores and SBP between two groups (Independent samples t-test/ Mann–Whitney U test) at six months will be applied. For differences in adherence scores and SBP in one group between two time points, a Paired samples t-test /Wilcoxon signed-rank test will be conducted on the data. P < 0.05 will be used as the significance test. Data will be reported as to why it is missing (Table-II). All analysis will be made using SPSS and R-Studio.

**Table-II T2:** Methods for data analysis

Independent variables (IDVs)	Dependent variables (DVs)	Type of analysis
Categorical (groups)	Continous (SEAMSscore)	(Independent samples t-test/ Paired samples t-test) (Wilcoxon signed-rank test/ Mann–Whitney U test)
Categorical (groups)	Continous (systolic blood pressure)	(Independent samples t-test/ Paired samples t-test) (Wilcoxon signed-rank test/ Mann–Whitney U test)
Categorical (all IDVs)	Categorical (all IDVs)	Chi-squared test

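### The planning values of 7.4 and 7.0 fit neither SEAMS nor the pill-count percentage, so the stated inputs do not justify 220 per arm for the primary outcome

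*Protocol article*

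**What the plan says.** All places are in the protocol article.

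- **Sample Size** says the calculation is meant "to detect between the two groups on the adherence change to the primary outcome measure". The planning values are: "The adherence score in the intervention group is 7.4, and in the control, it is 7.0". They are credited to a cited study, and the scale is not named. The error rate is given as "The alpha level is set at 0.05, a confidence interval of 95"%. The result is: "The calculated sample size is 220 in each group and 440 overall after a 30% attrition rate". The formula is a figure that is not available in the text reviewed.
- **Primary Outcome** defines the outcome as the change in adherence between baseline and six months: "The primary endpoint will be assessed using the SEAMS and pill counts used over a certain period".
- **Data Collection** describes SEAMS as a 13-item scale whose "scores go between 13 and 39". It describes pill count as tablets taken divided by tablets prescribed: "If the adherence percentage is 80% or higher, it will be considered adherent".
- **Statistical Analyses** (Table-II) lists "Continous (SEAMSscore") as the continuous adherence variable. The text compares the groups on adherence scores at six months.

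**The concern.** The sample size section says it addresses the primary outcome measure, but the means it uses lie below the lowest score a participant can obtain on SEAMS. They are not usable as pill percentages either. The 0.4 difference that drives the calculation is therefore not expressed in the units of any primary measure the article describes.

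What is at stake is the stated rationale for the trial's size. As written, a reader cannot tell what SEAMS difference, or what difference in the proportion adherent by pill count, the trial was designed to detect. Nor can a reader judge whether that difference would matter clinically.

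**Working it through.** **1. Compare the planning values with each primary measure.**

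| Measure | Scale in the article | Do 7.4 and 7.0 fit? |
|---|---|---|
| SEAMS score | 13 to 39 | No. Both are below the minimum, by 13 − 7.4 = 5.6 and 13 − 7.0 = 6.0 points |
| Pill count, percentage | adherent at 80% or more | Not sensibly. Both arms would sit 72.6 and 73.0 points below the cut, and nothing in the article supports this |
| Pill count, read as 74% v 70% adherent | proportion | Does not lead to 220 (step 4) |
| Change in SEAMS | at most 39 − 13 = 26 points | Possible arithmetically, but not what the text says (step 5) |

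**2. Try to reach the plan's 220.** The inputs from Sample Size are a difference of 7.4 − 7.0 = 0.4, alpha 0.05 (taken as two-sided) and 30% attrition. Allocation is 1:1. SD and power are not in the available text, so I solve for the SD under assumed power. For two means, n per arm = 2·SD²·(z_α + z_β)² / difference².

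- With 220 inflated as n/(1 − 0.30), n = 220 × 0.70 = 154. The standardised difference at 80% power is (1.960 + 0.842) × √(2/154) = 0.319, so the implied SD is 0.4/0.319 = 1.25. At 90% power it is (1.960 + 1.282) × √(2/154) = 0.369, and the implied SD is 1.08.
- With 220 inflated as n × 1.30, n = 169, since 169 × 1.30 = 219.7. The implied SD is 1.31 (80%) or 1.13 (90%).
- Forward check: SD 1.25 at 80% power gives 2 × 1.5625 × 7.849 / 0.16 = 153.3, so 154, and 154/0.70 = 220.

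The printed total can therefore be reached with a 0.4 difference and an SD slightly above 1. This shows one consistent route. It does not reproduce the original derivation, because SD and power were chosen to fit.

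**3. What 220 per arm delivers, whatever the original route.** If 30% of 220 are lost, 154 remain. From step 2, the detectable standardised difference at two-sided 0.05 is about 0.32 (80% power) or 0.37 (90%). In SEAMS points this is 0.319 × SD. No SEAMS SD is given, so these are assumed values: SD 2 gives 0.64, SD 3 gives 0.96, SD 4 gives 1.28 and SD 5 gives 1.60 points.

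**4. The 74% v 70% reading.** With pooled proportion 0.72 and 80% power, n = [1.960·√(2 × 0.72 × 0.28) + 0.842·√(0.74 × 0.26 + 0.70 × 0.30)]² / 0.04² = 1,977 per arm before attrition. This is far from 154 or 169.

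**5. The change-score reading.** The section mentions adherence change, and changes of 7.4 and 7.0 would be possible on a scale 26 points wide. But the text calls the values the score in each group. Read as changes, they would have the control arm, on conventional care only, gain 7.0 points. The SD of change would have to be about 1.25 points to arrive at 220 with 80% power. Nothing in the article supports either.

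**The case against.** The strongest reply is that the total may be adequate and that the article is a condensed account. Much of this stands, and it limits the point in several ways.

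- **The missing SD and power are no error here.** The formula is a figure that is not shown, and both values may be in it or in the full protocol. A reader might infer that the calculation was never properly specified. The available text does not support that.
- **The alpha wording is sound.** A level of 0.05 and a 95% confidence interval agree.
- **The attrition step is not shown to be wrong.** 154/0.70 and 169 × 1.30 both give 220. A reader might infer that power was lost through the second route, but that needs both that route and an 80% target, and the text states neither.
- **The trial is not shown to be underpowered.** A reader might carry the 0.4 difference to SEAMS. With 154 per arm, power would be Φ(0.4/(SD·√(2/154)) − 1.96) = 0.419, 0.215 and 0.140 at assumed SDs of 2, 3 and 4. This is illustration only. The SDs are assumed, and nothing makes 0.4 SEAMS points the target.
- **A null result would still be interpretable.** It would be read from the estimate and its confidence interval on the SEAMS scale, whatever the planning inputs were.
- **The origin of the values is not known.** It is a fair inference that they come from another instrument, but the cited study is not available. Only the mismatch with the article's own scales is certain.

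None of this removes the mismatch. The article prints specific planning values for the primary outcome measure, and its own description of that measure excludes them. That is a wrong stated input, not a detail left to a fuller document.

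**Conclusion.** The point holds in limited form. The values 7.4 and 7.0 cannot be SEAMS scores and do not fit the pill-count percentage with its 80% cut, and no section names a scale on which they are valid. The stated inputs therefore do not justify 220 per arm for the primary outcome.

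It would go too far to say that 220 per arm tells us nothing about that outcome: with 154 remaining per arm, about 0.32 SD is detectable at 80% power and about 0.37 SD at 90%. These figures assume two-sided alpha of 0.05, equal arms, 30% loss and the normal approximation. Whether 0.32 SD is a worthwhile SEAMS difference cannot be judged from the article, which gives neither an SD nor a target difference on that scale. The fault is in the stated justification. It does not by itself call for a different number of patients or a different analysis.

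**What to change.** Keep 440 and rewrite the Sample Size paragraph.

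1. Name the instrument and range behind 7.4 and 7.0, and stop presenting them as expected values of the primary outcome measure. Disclose them as the original basis; do not silently delete them.
2. Add a justification on the analysed scale, labelled as a restatement and not as the original derivation. Possible wording:

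> Restated justification: if 30% attrition leaves 154 of 220 participants per arm, the trial has 80% power at two-sided 0.05 to detect a standardised difference of about 0.32 (90% power for about 0.37) in the SEAMS score at six months. With an SD of [value and source], this equals [x] SEAMS points.

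3. Take the SD from a cited source or from the blinded pooled baseline data. Participants are selected for non-adherence on SEAMS and pill count, so the baseline SD may be smaller than the six-month SD; give a short range.
4. Give the matching detectable difference, at 154 per arm, for the proportion with at least 80% pill adherence, with the assumed control proportion.
5. Report how attrition was applied in the original calculation from the trial's own records. It should not be reconstructed from the total.

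The cost is one paragraph and a search for an SD. No patients are added and the analysis does not change. The downside is that the detectable effect, once in SEAMS points, may look less favourable than the present text suggests.

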### Randomization, Sequence generation, and Allocation concealment:

A simple, complete randomization technique will be used.^19^ Initially, the formula =ROUNDUP (RAND ()*440,0 will be used in Microsoft Excel to create a random sequence. Using their unique identification numbers, participants will be randomly assigned 1:1 into each group in a parallel manner. When the sealed opaque envelopes with the screened participants’ identification numbers are opened, it will be clear which group (control or intervention) they are assigned to. Every ongoing randomization phase will be carried out by a biostatistician.

### Blinding:

The data collectors and outcome evaluators will be unaware (blinded) of the group allocation. The flow chart (CONSORT) is provided in Fig.3.

**Fig.3 F3:**
[figure not shown]
Flow Chart.

### Data Collection:

A four section validated and pretested questionnaire in Urdu and English will be utilized. Section-A will involve the collection of data on pertaining to health and sociodemographics. Section B will be the the SEAMS-related scale.^20^ A 13 item measure called SEAMS is used to evaluate medication adherence.^20^ The scale’s scores go between 13 and 39. Greater levels of scores are correlated with better scores.

In Section-C, participants will be questioned about the number of pills used. The number of tablets taken over a certain time period divided by the total number of tablets prescribed for that time period was used to calculate the non-adherence rates.^16^ If the adherence percentage is 80% or higher, it will be considered adherent; if it is less than 80%, it will be regarded non-adherent. The literature also reports on this threshold. 14,16

Finally, Section-D will be a survey of the post-intervention follow-up to determine the intervention’s acceptability. At the final follow-up interview, participants in the intervention arm will be evaluated for end-user suggestions.

### Statistical Analyses:

Intention-to-treat analysis will be applied. The mean and standard deviation/ median and interquartile ranges will be presented. Frequencies and percentages will be used to depict categorical data. Differences in adherence scores and SBP between two groups (Independent samples t-test/ Mann–Whitney U test) at six months will be applied. For differences in adherence scores and SBP in one group between two time points, a Paired samples t-test /Wilcoxon signed-rank test will be conducted on the data. P < 0.05 will be used as the significance test. Data will be reported as to why it is missing (Table-II). All analysis will be made using SPSS and R-Studio.

**Table-II T2:** Methods for data analysis

Independent variables (IDVs)	Dependent variables (DVs)	Type of analysis
Categorical (groups)	Continous (SEAMSscore)	(Independent samples t-test/ Paired samples t-test) (Wilcoxon signed-rank test/ Mann–Whitney U test)
Categorical (groups)	Continous (systolic blood pressure)	(Independent samples t-test/ Paired samples t-test) (Wilcoxon signed-rank test/ Mann–Whitney U test)
Categorical (all IDVs)	Categorical (all IDVs)	Chi-squared test

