## METHODS

This study is 12 months duration long overall from January to December 2021, including six months follow up period, two-arm, single-blinded, intention-to-treat randomized controlled trial. The evaluation will be performed at the pretest and posttest. This trial is designed in accordance with the SPIRIT 2013 guidelines (Fig.1).^15^

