### Control Arm:

Participants in the control group receive conventional care only. No intervention/ placebo will be provided to controls. There will be no way to keep them engaged except follow-ups.

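### The article declares an intention-to-treat analysis and allows for 30% attrition, but the six-month tests it fixes can use only patients with a six-month value, so the claim is unsupported for everyone else

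*Protocol article*

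**What the plan says.** - **Label.** Methods describes a "two-arm, single-blinded, intention-to-treat randomized controlled trial", and Statistical Analyses repeats "Intention-to-treat analysis will be applied".
- **Expected loss.** Sample Size: "The calculated sample size is 220 in each group and 440 overall after a 30% attrition rate".
- **Visits.** Primary Outcome: "The adherence to antihypertensive medication will be assessed at baseline and six months". Secondary Outcome gives the same two time points for SBP, so there is one post-baseline measurement.
- **Test.** Statistical Analyses compares the arms at six months ("Differences in adherence scores and SBP between two groups") by independent-samples t-test or Mann-Whitney test, with no baseline covariate. Table-II lists the same tests for SEAMS and SBP.
- **Missing data.** The only sentence is "Data will be reported as to why it is missing". It points to Table-II, which contains tests and no handling rule.
- **Contact with controls.** Control Arm: "There will be no way to keep them engaged except follow-ups". The Intervention Arm section gives the other arm daily reminders, twice-weekly graphic messages and a weekly video.

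**The concern.** A two-sample test at six months needs a six-month value. With a single post-baseline visit there is no intermediate measurement to draw on, and the tests named do not use the baseline value either. Followed as written, the comparison leaves out every randomised patient who misses that visit. The article itself allows for this to be as many as 30%. Enlarging the sample for attrition protects power; it does not protect the comparison from selective loss.

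Selective loss is plausible here. Patients are enrolled because they are non-adherent, the outcome is adherence, and the arms differ in how much contact they receive. If patients who stop their tablets also tend to miss the final visit, and do so differently by arm, the observed difference mixes the effect of the package with the effect of who came back. An intention-to-treat label would suggest to readers that this had been dealt with.

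**Working it through.** **1. The plan's own figures.** Expected loss is 0.30 × 440 = 132 (66 per arm), leaving 308 (154 per arm). The stated size agrees with dividing by the retained fraction: 154 / 0.70 = 220. The SD and power are not in the text (the formula is a figure not shown), so the 220 cannot be reproduced. It can only be back-solved from the stated difference of 7.4 − 7.0 = 0.4. With two-sided alpha of 0.05 assumed, SD = 0.4 × √(154/2) / (1.96 + z for power). This gives about 1.25 at 80% power and 1.08 at 90%. The stated size therefore fits an analysis of about 154 observed patients per arm, under those assumed values.

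**2. Detectable effect.** With 154 per arm and an assumed 80% power: (1.96 + 0.84) × √(2/154) = 0.32 SD.

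**3. Bias when loss depends on the outcome.** Assumptions: standard normal six-month outcome, no true effect and 220 randomised per arm. The log-odds of loss rise by *b* per SD of lower adherence, with the intercept set to give each loss rate. Bias is the mean among observed intervention patients minus the mean among observed controls. Type I error is P(|Z + bias/SE| > 1.96), with SE from the observed patients.

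| Loss, intervention / control | *b* | Bias (SD) | Type I error |
|---|---|---|---|
| 30% / 30%, same mechanism | any | 0 | 5% |
| 25% / 35% | 1 | −0.08 | 12% |
| 20% / 40% | 1 | −0.16 | 32% |
| 20% / 40% | 0.5 | −0.09 | 13% |
| 20% / 40% | 0.25 | −0.05 | 7% |
| 30% / 30%, informative in intervention arm only | 1 | +0.25 | 63% |
| same | 0.5 | +0.14 | 25% |
| same | 0.25 | +0.07 | 10% |

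Example, 20% / 40% with *b* = 1: the observed means are 0.173 and 0.332, so the bias is −0.159. The observed variances are 0.888 and 0.841 on 176 and 132 patients, so SE = √(0.888/176 + 0.841/132) = 0.107. The ratio is −1.49 and the rejection rate 32%. If the SD is kept at 1 rather than reduced by the selection, the 32% and 63% become 28% and 60%.

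A slope of 1 places those lost about 0.84 SD below those observed; 0.5 corresponds to about 0.48 SD and 0.25 to about 0.25 SD. The documents give no basis for choosing among them.

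**4. A second parametrisation.** Take SD 1.25, 30% loss per arm, and control losses resembling control completers. If lost intervention patients score *g* SD below those observed, bias = 0.30 × *g* × 1.25. For *g* = 0.25, 0.5 and 1.0 this is 0.09, 0.19 and 0.375, or 23%, 47% and 94% of the planned 0.4. Type I error is about 10%, 26% and 75%.

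**5. What baseline adjustment can do.** When loss is unequal and driven by the baseline value (assumed baseline-to-outcome correlation 0.5, 20% / 40% loss, slope 1 on baseline), simulation under no effect gives the unadjusted test a bias of −0.08 SD and a type I error of 11%. The baseline-adjusted comparison has about zero bias and 5%.

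**The case against.** The strongest objection is scope. This is a condensed article. The analysis set, imputation and sensitivity analyses commonly sit in the full protocol or analysis plan, which are not shown. That stands against any bare complaint that a missing-data policy is absent. It does not dispose of this point, because the article itself fixes an unadjusted six-month test and itself says what will be done about missing data.

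A reader might infer that the trial will analyse completers only and that its result is not intention-to-treat. The documents do not support either statement. The analysis set is not defined, a t-test can be run on imputed data, and intention-to-treat may be used here to mean analysis by allocated arm. The text supports only that the claim is not backed for patients without the visit.

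Three further objections stand. The 30% is a planning allowance, not observed loss. The control-arm sentence excepts follow-ups, the very contact that produces the six-month value, so higher loss among controls is plausible but not shown. The larger error rates need a steep slope, and the largest need informative loss in one arm only. The scenarios also point in opposite directions, so no direction of bias is established.

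Finally, imputation from baseline assumes that loss is explained by baseline data. It would not fully remove the bias in step 3, where loss depends on the six-month outcome itself. Because enrolment requires baseline adherence below 80%, baseline may also predict less well than usual.

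**Conclusion.** The point holds in limited form. For up to 132 of 440 randomised patients, the article's intention-to-treat claim is not backed by the tests and the missing-data statement it gives.

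Bias is a possibility whose size depends on assumptions outside the documents. With no true effect it is zero when loss is unrelated to outcome or follows the same mechanism and rate in both arms. For slopes of 0.5 to 1 per SD it is about 0.09 to 0.16 SD at 20% versus 40% loss, and 0.14 to 0.25 SD if loss is informative in one arm only. Against 0.32 SD, that is 0.09/0.32 = 28% to 0.25/0.32 = 78% of the detectable effect. The upper figures should be read as illustrations and not as a forecast of a false-positive rate.

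The change is worth making because the article commits to an unadjusted test, while a better one is available from data already collected.

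**What to change.** - State that all randomised participants are analysed in their allocated arm.
- Replace the unadjusted six-month test with a baseline-adjusted comparison (ANCOVA). Multiply impute missing six-month values within arm from baseline SEAMS, pill percentage, SBP and the Section-A variables.
- Add a delta-adjusted sensitivity analysis that lowers imputed values separately by arm, because imputation from baseline removes only the bias that baseline predicts.
- Report attrition by arm as well as the reasons for it, and keep the observed-data comparison as a sensitivity analysis.
- If only patients with a six-month value are analysed, describe the result as an available-case analysis by allocated arm, not as intention-to-treat.

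If the full analysis plan already contains such a rule, one sentence in the article settles the matter. No new data are needed, and R is already among the planned software. The cost is slightly more analysis work and possibly slightly wider intervals.
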